## Abstract

**Background:**

Diabetic retinopathy (DR) and diabetic macular edema (DME) are potentially blinding, microvascular retinal diseases in people with diabetes mellitus. Preclinical studies support a protective role of the hormone prolactin (PRL) due to its ocular incorporation and conversion to vasoinhibins, a family of PRL fragments that inhibit ischemia-induced retinal angiogenesis and diabetes-derived retinal vasopermeability. Here, we describe the protocol of an ongoing clinical trial investigating a new therapy for DR and DME based on elevating the circulating levels of PRL with the prokinetic, dopamine D2 receptor blocker, levosulpiride.

**Methods:**

It is a prospective, randomized, double-blind, placebo-controlled trial enrolling male and female patients with type 2 diabetes having DME, non-proliferative DR (NPDR), proliferative DR (PDR) requiring vitrectomy, and DME plus standard intravitreal therapy with the antiangiogenic agent, ranibizumab. Patients are randomized to receive placebo (lactose pill, orally TID) or levosulpiride (75 mg/day orally TID) for 8 weeks (DME and NPDR), 1 week (the period before vitrectomy in PDR), or 12 weeks (DME plus ranibizumab). In all cases the study medication is taken on top of standard therapy for diabetes, blood pressure control, or other medical conditions. Primary endpoints in groups 1 and 2 (DME: placebo and levosulpiride), groups 3 and 4 (NPDR: placebo and levosulpiride), and groups 7 and 8 (DME plus ranibizumab: placebo and levosulpiride) are changes from baseline in visual acuity, retinal thickness assessed by optical coherence tomography, and retinal microvascular abnormalities evaluated by fundus biomicroscopy and fluorescein angiography. Changes in serum PRL levels and of PRL and vasoinhibins levels in the vitreous between groups 5 and 6 (PDR undergoing vitrectomy: placebo and levosulpiride) serve as proof of principle that PRL enters the eye to counteract disease progression. Secondary endpoints are changes during the follow-up of health and metabolic parameters (blood pressure, glycated hemoglobin, and serum levels of glucose and creatinine). A total of 120 patients are being recruited.

**Discussion:**

This trial will provide important knowledge on the potential benefits and safety of elevating circulating and intraocular PRL levels with levosulpiride in patients with DR and DME.

**Ethics and dissemination:**

Ethics approval has been obtained from the Ethics Committees of the National University of Mexico (UNAM) and the Instituto Mexicano de Oftalmología, I.A.P. Dissemination will include submission to peer-reviewed scientific journals and presentation at congresses.

**Clinical trial registration:**

Registered at www.ClinicalTrials.gov, ID: NCT03161652 on May 18, 2017.

## Background

Diabetic retinopathy (DR) and diabetic macular edema (DME) are leading causes of blindness in adults under 75 years, and nearly all type 1 diabetic patients and more than 60% of type 2 diabetes patients have evidence of DR 15–20 years after diagnosis (1, 2). DR damages the integrity of retinal microvessels and progresses from a nonproliferative (NPDR) to a proliferative vascular stage (PDR). NPDR begins with abnormal capillary permeability and exudative changes that impair vision when the macula is affected (DME). PDR develops when occlusion of retinal capillaries creates areas of ischemia that promote the proliferation of blood vessels (angiogenesis) in the surface of the retina. The new blood vessels impair vision by bleeding into the vitreous, and ultimately lead to blindness by causing traction retinal detachment. Clinically important risk factors for progression to vision loss include hyperglycemia, hypertension, and dyslipidemia (1). However, the combined values of these parameters account for only 10% of the risk of DR (3–5). Laser therapy is partially effective for preserving sight, destroys retinal tissue, and is poor for reversing visual loss (6). Anti-angiogenic therapies are effective and less destructive but require frequent intravitreal delivery, which raises the risk of infection and ocular complications (7). Therefore, the prevention and treatment of DR and DME should explore other modifiable factors and less invasive modes of administration. The current trial investigates the potential benefits and safety of elevating the serum levels of prolactin (PRL) by the oral administration of the prokinetic, dopamine D2 receptor blocker, levosulpiride.

Prolactin, the pituitary hormone essential for lactation, can protect against DR and DME *via* its proteolytic conversion to vasoinhibins, a family of PRL fragments that inhibit the proliferation, permeability, and dilation of blood vessels (8). The generation of vasoinhibins regulated at the hypothalamus, the pituitary, and the target tissue levels defines the PRL/vasoinhibin axis (9). This axis participates in maintaining corneal avascularity (10) and normal retinal vasculature (11), and is altered in retinopathy of prematurity (12) and in DR (13). Vasoinhibins are reduced in the circulation of patients with DR (14) and preclinical studies show that raising systemic PRL levels leads to vasoinhibin accumulation in the retina (15). The elevation of intraocular vasoinhibins inhibits ischemia-induced retinal angiogenesis (16) and prevents and reverses diabetes-induced blood retinal barrier breakdown by targeting excessive vasopermeability (15, 17–19) and the outer component of the blood retinal barrier (retinal pigment epithelial cells) (20). Moreover, retinal neurodegeneration influences DR (4, 21) and PRL, itself, is a retinal trophic factor. Raising circulating PRL levels reduces retinal cell death and dysfunction in the continuous light-exposure model of retinal degeneration (22). Therefore, it is hypothesized that medications causing hyperprolactinemia result in increased ocular PRL and vasoinhibins levels with beneficial outcomes in DR and DME, because of the antagonizing properties of both hormones on diabetes-induced retinal alterations.

Levosulpiride is an effective medication for inducing hyperprolactinemia (23). It works as potent prokinetic in dyspeptic syndromes including diabetic gastroparesis, a complication found in 5% of diabetic patients (24, 25). The prokinetic effect of levosulpiride is mediated through blockage of enteric inhibitory dopaminergic D2 receptors, and D2 receptor antagonism at the anterior pituitary level evokes hyperprolactinemia (26).

A randomized, double-blind, placebo-control trial has been implemented with the aim to investigate the therapeutic potential and safety of levosulpiride in patients with DR and in DME patients treated or not with standard antiangiogenic therapy (ranibizumab). This paper describes the methodology and specific details underlying the study.

## Methods/Design

### Study Setting and Sample

A total of 120 patients will be enrolled in this study over the course of 3 years. Recruitment takes place at an out-patient clinical Institution [Mexican Institute of Ophthalmology, Private Assistance Institution (Instituto Mexicano de Oftalmología, I.A.P.), Queretaro, Mexico] at the time of a routine health care or with patients referred from other out-patient clinics and health facilities. The principal investigators or investigators inform the patients (orally and in writing) about benefits and risks of participating in the study and of the clinical assessments and randomized allocation of treatment. Patients have to provide written consent before being enrolled and prior the initiation of any study-related assessment. Patients may withdraw their consent to participate at any time without providing a reason. There is no financial compensation for the study participation. However, all clinical evaluations and study medication have no cost for the patients.

Based on the current status, we expect a screening rate of 600 patients in 3 years, out of which about 120 are expected to meet the inclusion criteria, be willing to participate and, therefore, enrolled in the study. The dropout rate is expected to be less than 20%. The study may expand to a multicenter format if not enough patients are recruited.

### Study Design

The study design is shown in Figure 1. This is a single-center, prospective, randomized, placebo-controlled, double-blind clinical trial on the efficacy and safety of levosulpiride for the treatment of DR and DME. An eight-armed study design is followed in which diabetic male and female subjects are selected from four different populations, those having DME, NPDR, PDR undergoing vitrectomy, and DME that will receive antiangiogenic therapy with ranibizumab. Ranibizumab is a humanized monoclonal antibody fragment directed against all forms of vascular endothelial growth factor (VEGF) approved as antiangiogenic therapy for DME (27). Immediately after baseline, each of the four groups is randomly split up into a subgroup that receives levosulpiride and a subgroup that receives placebo (lactose pill). Allocation is randomly assigned *via* computer-generated random numbers. The comparison of ophthalmologic and health outcomes between groups 1 and 2 (DME: placebo and levosulpiride) and groups 3 and 4 (NPDR: placebo and levosulpiride) will evaluate the efficacy and safety of the medication against DME and NPDR, respectively. Comparison between groups 7 and 8 (DME plus ranibizumab: placebo and levosulpiride) will investigate the benefits of levosulpiride treatment on top of standard antiangiogenic therapy with ranibizumab in advanced DME. Although anti-VEGF agents are the firstline therapy for DME involving the central macula, approximately 50% of the patients do not respond suggesting the contribution of other vasoactive and proinflammatory mediators (28). Vasoinhibins block the vascular effects of VEGF and of other cytokines present in the vitreous of DR patients (17, 18, 20, 29), implying that levosulpiride may extend and potentiate the benefits of the anti-VEGF therapy. The comparison of serum and vitreous PRL levels between the groups 5 and 6 undergoing vitrectomy (DR: levosulpiride and placebo) will serve as a proof of principle that PRL enters the eye to counteract disease progression. Blood samples are drawn immediately prior to surgery and before the induction of anesthesia.

**Figure 1 F1:**
[figure not shown]
Study design. ETDRS, Early Treatment Diabetic Retinopathy Study; OCT, optical coherence tomography; HbA1c, glycated hemoglobin; ALT, alanine aminotransferase; TSH, thyroid-stimulating hormone; DME, diabetic macular edema; TID, three times a day; NPDR, non-proliferative diabetic retinopathy; PDR, proliferative diabetic retinopathy.

### Eligibility Criteria

#### Inclusion Criteria

Age equal or greater than 40 years but no older than 69 yearsMale and female subjects with DMEMale and female subjects with NPDRMale and female subjects with PDR undergoing medically prescribed vitrectomyMale and female subjects with DME, with or without DR, requiring ranibizumabSigned informed consent

#### Exclusion Criteria

Not meeting inclusion criteria.History of ocular complications: severe myopia (>6 diopters), opacity of ocular media, glaucoma, ocular surgeries, and retinal detachment (except for PDR with vitrectomy)With retinal laser photocoagulation and/or intravitreal antiangiogenic therapy (<6 months before enrollment) (groups 1–4)With retinal laser photocoagulation and/or intravitreal antiangiogenic therapy (<6 weeks before enrollment) (groups 7 and 8)Prolactin serum levels >20 ng/mLLoss of kidney function (glomerular filtration rate <60 mL/min) for groups with DME, NPDR, and DME plus ranibizumabLoss of kidney function (glomerular filtration rate <30 mL/min) for groups with PDR undergoing vitrectomyContraindications for the use of levosulpiride (Parkinson’s disease, epilepsy, breast cancer, alcoholism, hypokalemia)Conditions inducing hyperprolactinemia including pathologies (hypothyrodism, hepatic dysfunction, prolactinomas) and medication (antipsychotics, antidepressants, prokinetics, estrogens, other)

#### Elimination Criteria

Worsening of disease requiring conventional treatmentNot complying with study medication (monitored by drug tablet return and the measurement of the circulating levels of PRL)Hesitation to continue with study medicationVoluntary withdrawal of consentInability to continue in-hospital appointmentsRelocation to another state or countryMissing outcome data

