### Blinding

Physicians (primary investigators and investigators) enroll the patients. An investigator (coordinator) fully knowledgeable of all protocols, policies, procedures, and definitions in the study allocates the treatment. Patients, care providers, and evaluators are blind to treatment allocation. Unblinding is permissible only in the case of significant improvement or significant deterioration of primary outcome measures. Interim analyses will be performed by the study coordinator and the principal investigator not involved in the direct evaluation of patients.

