### Data Collection and Analysis

The same physicians (ophthalmologists and endocrinologists) and laboratory technicians will collect and evaluate the data from all patients. Data are recorded in questionnaires, images and electronic quantitations (OCT, fundus biomicroscopy and fluoroangiography), and laboratory biochemical determinations. All images collected during the study are sent for re-assessment to a central evaluation center at the recruiting Institution to insure accurate evaluation. The coordinator of the study will continually examine the registry to insure all collected data are complete, accurate, and valid. Data logically inconsistent will be confronted with information in external database. Data collected on formatted paper forms are entered into a computer and electronic registries carefully reviewed by a third party to identify missing data, invalid or erroneous entries, and inconsistent data. Any data review activity and remediation efforts will be documented. Statistical methods evaluate continuous and categorical variables, the association between hormonal levels and outcome, and the relative contribution of confounding factors. The study data will be stored in the recruiting Institute through private accessing codes and kept for up to 10 years following the publication of the study. The data information will then be destroyed.

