### Safety Considerations

Levosulpiride is clinically approved and available in different countries (Italy, Spain, Germany, Belgium, Mexico, South Korea, etc). It is used at low doses (25–75 mg/day) as a prokinetic agent for the treatment of dysmotility-like functional dyspepsia (35, 36). It penetrates the blood–brain barrier poorly (37) so higher doses (800–2400 mg/day) are required for its use as an anti-depressant and anti-psychotic agent (38). Duration of treatment ranges from 1 week to more than 2 years (23). Low doses of levosulpiride are well tolerated during both acute and chronic administration. Heart rate and electrocardiogram are not altered (35) and sedation is rare (36). As the pituitary is outside the blood–brain barrier, low doses of levosulpiride increase serum PRL (39). Adverse effects of hyperprolactinemia include decreased libido, amenorrhea and infertility, breast engorgement and lactation, and gynecomastia (40). In a multicenter, double-blind, placebo-controlled trial of 408 dyspeptic patients receiving oral levosulpiride (25-mg TID for 4 weeks) the total incidence of hyperprolactinemia related disorders was 7% in female patients (41). More recently, a study in 342 dyspeptic female and male patients, using the same levosulpiride treatment, reported 40 patients (11%) with adverse effects (26.7% galactorrhea, 17.8% somnolence, 11% fatigue, and 11.5% headache), none of whom abandoned the study due to side effects (36).

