### Current Status

Patients started enrolling in this trial on May 2016. As of January 2018, 270 patients were screened and 63 identified as candidates signed the informed consent. Later nine patients were excluded (1 due to hyperprolactinemia, 6 because of glomerular filtration rates <30 mL/min, 1 due to glaucoma, and 1 requiring laser therapy). From the remaining 54 study subjects, 9 dropped-out after randomization (3 did not comply with the study medication, 2 missed outcome data, 1 required conventional therapy, and 3 vitrectomies were rescheduled as patients forgot to take hypertension medication before surgery and had very high blood pressure values), and 45 completed the study. Relevant protocol modifications will be registered at ClinicalTrials.gov. The protocol last amendment was registered on October 3, 2017 and consisted in the inclusion of DME patients receiving placebo or levosulpiride on top of standard antiangiogenic therapy with ranibizumab.

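### Circulating prolactin helps decide who is eliminated as non-compliant, yet it is the drug's direct effect and a primary outcome in groups 5 and 6, so the rule can remove low values from the levosulpiride arm only

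*Protocol article*

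**What the plan says.** Under Elimination Criteria, the protocol article lists non-compliance with study medication as a ground for elimination, "monitored by drug tablet return and the measurement of the circulating levels of PRL". It gives no PRL threshold and does not say how the two monitors are combined.

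Primary Outcome Measures lists serum and vitreous PRL. The abstract's Methods paragraph ties them to the vitrectomy groups: "Changes in serum PRL levels and of PRL and vasoinhibins levels in the vitreous between groups 5 and 6" are the proof of principle. Safety Considerations states that "low doses of levosulpiride increase serum PRL".

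Blinding says: "Patients, care providers, and evaluators are blind to treatment allocation". A coordinator allocates treatment. The same section adds: "Unblinding is permissible only in the case of significant improvement or significant deterioration of primary outcome measures". A compliance check is not among those reasons. Data Collection and Analysis says: "The same physicians (ophthalmologists and endocrinologists) and laboratory technicians will collect and evaluate the data from all patients".

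Current Status shows that elimination for non-compliance already happens after randomisation. Of 54 patients, "9 dropped-out after randomization (3 did not comply with the study medication" and 6 for other reasons), and the 45 completers are counted without them.

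**The concern.** One variable has three roles: it tests compliance, it is the drug's pharmacodynamic effect, and it is a primary outcome. A rule that removes patients after randomisation should work the same way in both arms and should not depend on the outcome. This one can fail on both counts.

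The PRL comparison in groups 5 and 6 is most exposed. It is meant to show that the drug raises PRL in serum and in the eye, and removing low values on the drug side moves it towards that conclusion. A smaller effect could reach visual acuity and the other ocular outcomes if they are correlated with PRL. Blinding is the second exposure, because a PRL value cannot be read as evidence of compliance without knowing which tablet the patient was given.

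**Working it through.** **Inputs from the protocol article**
- Baseline PRL is at most 20 ng/mL in both arms, since higher values are excluded (Exclusion Criteria).
- Placebo is a lactose pill; levosulpiride raises PRL (abstract; Safety Considerations).
- Groups 5 and 6 have one visit after enrolment, at vitrectomy, with blood drawn just before surgery (Outcome Measures; Study Design).
- 54 randomised, 9 lost, 3 of them for non-compliance, 45 completed (Current Status).
- 120 patients, eight arms (Study Setting and Sample; Study Design).
- Visual acuity: difference of 10 letters, SD 10 (Sample Size).

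**Step 1: is the PRL monitor symmetric?** A compliant placebo patient should have an unraised PRL, and so should a non-compliant one. PRL therefore says nothing about compliance on placebo. On levosulpiride an unraised value points to missed tablets or to a weak response. The monitor can only act in the levosulpiride arm, and only on low values.

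**Step 2: is it separate from the outcome?** In groups 5 and 6 the stated schedule gives one PRL measurement after the start of treatment, and that measurement is the endpoint. Any PRL-based exclusion there uses the endpoint value itself.

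**Step 3: what has been observed?** Lost for non-compliance: 3/54 = 5.6%. All losses: 9/54 = 16.7%, within the expected dropout of under 20%. Non-compliance is 3/9, or one third, of the losses. Arm, group and ground (tablets or PRL) are not given.

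**Step 4: how large could the shift be?** The article states no figure to reproduce, so this is an illustration. Assume that PRL on a suitable scale is normal, that the lowest fraction p of the levosulpiride arm is removed on PRL alone, and that nothing is removed from placebo. The arm's mean then rises by φ(z_p)/(1 − p) SD:

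| p removed | Shift in mean (SD) |
|---|---|
| 10% | 0.1755/0.90 = 0.195 |
| 20% | 0.2800/0.80 = 0.350 |
| 30% | 0.3477/0.70 = 0.497 |

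As a bound on what has been seen, suppose that all 3 non-compliers were on levosulpiride and removed purely on PRL. With 54/2 = 27 patients per arm under 1:1 allocation, p = 3/27 = 11% and the shift is about 0.21 SD. The 20% and 30% rows go beyond anything observed.

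**Step 5: effect on a test.** The number per arm stands only in the figure, so take 120/8 = 15 as an assumption. Simulating two arms with no true difference, removing the lowest values from one arm only and applying a two-sided t-test at 5% gives:

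| Removed of 15 | Bias (SD) | Rejection rate |
|---|---|---|
| 1 | 0.12 | 7.2% |
| 2 | 0.23 | 10.9% |
| 3 | 0.33 | 15.7% |

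Levosulpiride is expected to raise serum PRL, so no true difference is an artificial setting. The table shows how one-sided removal acts; it does not predict this trial's error rate.

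**Step 6: spill-over to visual acuity.** The bias is roughly correlation × PRL shift × SD of acuity. With p = 10% and an assumed PRL–acuity correlation of 0.3 to 0.5, it is 0.3 × 0.195 × 10 = 0.6 to 0.5 × 0.195 × 10 = 1.0 letters, against a planned difference of 10.

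**The case against.** The other side has a good deal to say, and much of it stands.

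- **Fully adherent patients.** A reader might infer that patients who took every tablet but showed little PRL rise will be removed. The article does not say so. PRL is one of two monitors, and nothing states that it overrides a full tablet count.
- **Selected responders against all placebo patients.** This reading is also tempting and goes too far. Tablet return works in both arms, so placebo non-compliers can be eliminated too. Only the PRL part of the rule is one-sided.
- **Blinding already lost.** The article does not establish this. The coordinator who allocates treatment also examines the registry and could apply the PRL check alone. Using the same physicians and technicians for all patients describes consistency; it does not say that image graders see PRL results. All images are also re-assessed centrally. A condensed article may leave masking of laboratory results to the full protocol.
- **Different groups, different harms.** By the abstract, PRL is the endpoint in groups 5 and 6, while the other groups have ocular endpoints. Selection on the outcome and exposure of graders fall mainly in different groups.
- **Recoverability.** In groups 5 and 6 serum PRL must have been measured before anyone could be excluded on it, so the value exists and the analysis set can still include it.
- **Size.** The shift rests on assumptions, and the article gives no PRL effect or SD against which to judge 0.2 SD.

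None of this removes the core. The criterion as written lets a primary outcome, informative about compliance in one arm only, decide who is eliminated. If the coordinator applies it alone, the blinding risk is contained but the one-sided selection is not.

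**Conclusion.** The concern holds in a limited form. Elimination rests partly on circulating PRL, which is both the drug's direct effect and a primary outcome in groups 5 and 6, and low PRL can count against a patient only on levosulpiride. To the extent that PRL drives elimination, the PRL comparison is biased in favour of the drug.

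The size in this trial is unknown. About 0.2 SD is a reasonable illustration for removal of the lowest 10% of the levosulpiride arm. It assumes normality, removal strictly by lowest PRL and no matching removal on placebo. Under the assumed correlations the effect on visual acuity is small, about 0.6 to 1.0 letters.

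Loss of blinding is a risk and not an established fact. It depends on whether anyone other than the allocating coordinator sees post-baseline PRL. The 3 non-compliers cannot be called wrongly removed, because their arm and the ground for elimination are not reported.

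**What to change.** 1. Remove PRL from the elimination criterion. Monitor compliance by tablet return, by the same rule in both arms.
2. Keep every randomised patient with outcome data in the assigned arm for the primary comparison. Check the 3 patients already lost for non-compliance, and include any who were eliminated on PRL and whose outcome data exist. Do not presume that all three qualify.
3. Withhold post-baseline PRL values from blinded clinicians and evaluators until database lock.
4. Use PRL-based adherence only in an exploratory exposure analysis, labelled as such.

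The cost is an amendment to the criterion, an instruction to the laboratory on who receives results, and a review of the records of the three patients. Since 45 patients had completed by January 2018, the report should say which of them were followed under the existing criterion. The downside is that compliance is measured slightly less precisely, because tablet counts alone cannot show that tablets were swallowed.
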